### Ethical considerations

Full ethical approval has been obtained by the Medical Ethics Committee of The University of Queensland (2011000553), The Royal Children’s Hospital Brisbane (HREC/11/QRCH/37) and The Cerebral Palsy League Ethics Committee (CPL-2012-004). Trial registration has been obtained with the Australian and New Zealand Clinical Trials Registry: (ACTRN12613000181707). Informed, written consent will be obtained from all parents or guardians and assent from participants (if 12 years of age or older) before entering the trial.

### Study sample and recruitment

Fifty children and youth with spastic hemiplegia aged 5–16 years will be recruited across Queensland, Australia. Potential study participants will be identified through a population-based research database, which currently comprises of over 1300 children with CP at the Queensland Cerebral Palsy and Rehabilitation Research Centre (QCPRRC), the Queensland Cerebral Palsy Register (QCPR), Queensland CP Health Service, Queensland Cerebral Palsy League and advertising to Occupational Therapists, Physiotherapists and Paediatricians at the Royal Children’s Hospital, Brisbane and in the community. The recruitment process will target both publicly funded services and private practitioners with the expectation that the sample will be representative of children with congenital hemiplegia.

### Inclusion criteria

The study will include school aged children and youth:

(1) With a confirmed diagnosis of congenital hemiplegia.

(2) Aged five to 16 years.

(3) Who have reduced upper limb function due to predominant spasticity rather than dystonia.

(4) Who can provide sufficient co-operation and cognitive understanding to participate in the therapy activities.

For a subset of children performing the Advanced Brain Imaging studies further inclusion criteria are:

i Sufficient co-operation to perform Advanced Brain Imaging studies for 45 minutes.

ii No exclusions for 3 Tesla Magnetic Resonance Imaging (3T MRI) including no metal implants, no shunts, no uncontrolled epilepsy as the later would be a confound.

### Exclusion criteria

Participants will be excluded if they have:

(1) Fixed contracture or severe muscle spasticity in the designated muscle groups.

(2) Previously undergone surgery in the upper limb (UL).

(3) Received BoNT-A injections within six weeks prior to baseline assessments.

### Sample size

The primary basis for sample size calculation for this study is adequate power for the primary hypothesis: H^1^ comparison between the functional effects of COMBiT compared to standard care at 26 weeks. Based on data from the previous study [25] a mean difference of 7 units (10% of the control group mean at baseline on the Melbourne Assessment of Unilateral Upper Limb Function (MUUL) is proposed as the minimum difference likely to have clinical implications [27,28]. We assume a standard deviation of 9 units. Based on a comparison with alpha = 0.05 and 80% power, 25 subjects in each group (n=50) are required.

For H^2^, our previous upper limb has shown 90% success on 3 repeated fMRI scans [25]. Using 3T fMRI we can see activation in the representative cortex for motor studies with good signal to noise ratio. We allow for some loss of information due to subject refusal (10%) and scans where motion is a confounder (10%). With 40 participants in an analysis of baseline to week 13 changes on fMRI, this study will have 80% power to detect a difference between groups of 0.9 SDs. If we consider the supplementary motor area (SMA) given coefficients of variation (COV) for control subjects performing motor tasks (COV of 11% in PM1 and 35% in SMA) [29] and activation signal of 1.5%, we are able to detect differences in percentage activation levels over time as small as 0.47.

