**Methods and analyses:**

A total of 50 children (25 in each group) with congenital hemiplegia will be recruited to participate in this randomized comparison trial. Children will be matched in pairs at baseline and randomly allocated to receive an intensive block group hybrid model of combined mCIMT followed by intensive bimanual training delivered in a day camp model (COMBiT; total dose 45 hours direct, 10 hours of indirect therapy), or a distributed model of standard occupational therapy and physiotherapy care (SC) over 12 weeks (total 45 hours direct and indirect therapy). Outcomes will be assessed at 13 weeks after commencement, and retention of effects tested at 26 weeks. The primary outcomes will be bimanual coordination and unimanual upper-limb capacity. Secondary outcomes will be participation and quality of life. Advanced brain imaging will assess neurovascular changes in response to treatment. Analysis will follow standard principles for RCTs, using two-group comparisons on all participants on an intention-to-treat basis. Comparisons will be between treatment groups using generalized linear models.

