### Randomisation

Following baseline assessments, children will be randomised within matched pairs to receive either COMBiT or standard care. To maximise homogeneity of the sample and minimise group differences at baseline, matching in pairs will be completed according to age (12 month bands), gender, and Manual Ability Classification System (MACS) level [30]. Treatment allocation will be recorded on a piece of folded paper inside a concealed opaque envelope. Using a sequence of computer-generated random numbers the number “1” or “2” will be allocated to each member of the pair. As each pair is randomised, they will be allocated the next consecutive envelope, which will be opened by non-study personnel who will read and record the treatment allocation. Study personnel will be informed of group allocation.

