### Study interventions

For the COMBiT day camp group, we plan to provide treatment in groups of 10–15 children over ten days. The initial five consecutive days will focus on mCIMT. After a weekend, BIM will be provided for the next five consecutive days. Therapy will comprise 45 hours direct upper limb training and 10 hours of indirect training in more general gross motor upper limb activities. COMBiT will have a novel circus theme. This intensive COMBiT therapy will be compared to standard care which involves individually tailored therapy in a distributed model for 1.5 hours per week for six weeks. This involves six hours individual therapy with OT/PT and three hours of home program demonstration (nine hours direct UL therapy). The home programs (completed by participants in their home/community environment) will comprise 30 minutes daily home practice six days/week for 12 weeks (36 hours indirect UL therapy). The COMBiT and the standard care programs will have the same dosages of upper limb therapy (COMBIT: 45 hours direct UL training; Standard care (SC): nine hours direct UL training and 36 hours indirect UL therapy). They will differ by (i) delivery method (block, group model versus distributed individualised model) (ii) varied construct (mCIMT versus goal directed training) and (iii) different environment.

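### The 80% power stated for H1 has no margin: the 50 children required at 26 weeks are exactly the 50 recruited, with no allowance for loss

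*Protocol article*

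**What the plan says.** The Sample size section sizes the trial on H1, described as the "comparison between the functional effects of COMBiT compared to standard care at 26 weeks". The inputs are "a mean difference of 7 units (10% of the control group mean at baseline" on the MUUL, and "We assume a standard deviation of 9 units". It concludes: "Based on a comparison with alpha = 0.05 and 80% power, 25 subjects in each group (n=50) are required". It names neither a formula nor the sidedness of the test, and it does not say whether the SD is before or after adjustment for baseline or matching.

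The abstract says "A total of 50 children (25 in each group) with congenital hemiplegia will be recruited", and Study sample and recruitment also gives fifty. The number required for analysis is therefore the number enrolled.

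For the imaging hypothesis H2, the same section does make an allowance: "We allow for some loss of information due to subject refusal (10%) and scans where motion is a confounder (10" (the second figure is also 10%), which leaves 40 analysed.

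Under Statistical analyses, the primary analysis uses evaluable data, and imputation for non-ignorable missingness is kept for sensitivity analyses. The model is a generalized linear model with terms for matching and, as a possibility only, for confounders such as baseline unimanual capacity. No camp term is named.

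Under Randomisation, "children will be randomised within matched pairs to receive either COMBiT or standard care". For COMBiT delivery, Study interventions says "we plan to provide treatment in groups of 10–15 children over ten days". Standard care is given individually.

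**The concern.** If 50 children are needed at 26 weeks and 50 are enrolled, a single child without a 26-week score takes the trial below its own stated requirement. The analysis section expects some children to be missing, so the sizing and the analysis rest on different assumptions about completeness.

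What is at stake is how a null result would be read. The protocol calls 7 units the smallest difference likely to matter clinically. A non-significant 26-week comparison would be set against 80% power for that difference, when the stated inputs with modest loss give nearer 70%.

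A secondary issue is that children in the same day camp share staff, activities and peers, and children in standard care do not. Any camp effect would add variance in one arm only. Neither the power figure nor the described model mentions it.

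**Working it through.** **Inputs from the Sample size section:** difference 7, SD 9 (standardised difference 7/9 = 0.778), alpha 0.05, power 80%, 25 per group. Two-sided testing is my assumption.

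**1. Reproducing the stated figure.** Normal approximation: n per group = 2 × (1.96 + 0.8416)² × (9/7)² = 25.95, so 26 after rounding up, against 25 stated. By the noncentral t, n = 26.94, so 27. At 25 per group the standard error is 9 × √(2/25) = 2.546, so 7/2.546 = 2.750 and power = Φ(2.750 − 1.960) = 78.5%. The t-test gives 76.9%. The stated figure is reproduced to within rounding and choice of formula.

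**2. Adding loss.** The document gives no expected loss for H1, so 10% and 20% are assumptions, applied equally to both arms.

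| Assumed loss | n per group | Power, normal | Power, t-test | Difference detectable at 80%, t-test |
|---|---|---|---|---|
| 0% | 25 | 78.5% | 76.9% | 7.3 |
| 10% | 22.5 | 74.2% | 72.2% | 7.7 |
| 20% | 20 | 69.1% | 66.9% | 8.2 |

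**3. Crediting baseline adjustment.** If 9 is an unadjusted SD and the baseline score correlates r with the 26-week score, the residual SD is 9 × √(1 − r²). The document gives no r, so a range is shown (t-test).

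| Assumed r | Residual SD | No loss | 10% loss | 20% loss |
|---|---|---|---|---|
| 0.3 | 8.59 | 80.6% | 76.2% | 71.0% |
| 0.5 | 7.79 | 87.5% | 83.8% | 79.0% |

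**4. Camp clustering (secondary).** With 25 COMBiT children in camps of 10–15 there would be about two camps, so m = 12.5. With intraclass correlation ρ in that arm only, its variance is multiplied by 1 + 11.5ρ, and the variance of the difference by (2 + 11.5ρ)/2. No ρ is given, so the values are assumed. Power uses the normal approximation with no loss, and the figure to compare with is 78.5%.

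| Assumed ρ | Variance ratio | True SE relative to reported | Power |
|---|---|---|---|
| 0.02 | 1.115 | 1.06 | 74.0% |
| 0.05 | 1.2875 | 1.13 | 67.9% |

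The true SE would be 6% to 13% larger than reported. Put the other way, the reported SE would be about 5% to 12% too small (1 − 1/1.056 and 1 − 1/1.135).

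**The case against.** Four stronger readings are tempting, and the document does not support them.

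*That the sample size is an arithmetic error.* A reader might infer this from 26 or 27 against 25. But 25.95 rounded down to 25 costs about 1.5 points of power by the normal approximation, and the remaining gap to 76.9% comes from using the t-test. That would not merit action alone. It only shows that the figure has no slack.

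*That 80% power will not be delivered.* This holds only for an unadjusted comparison. The planned model includes matching terms and may include baseline, and at an assumed r of 0.5 power is still about 84% after 10% loss. This objection largely stands. What remains is that the baseline term is optional, no correlation is stated, and the meaning of the SD is not given. At r = 0.3 with 10% loss the figure is 76%. An adjustment that is neither committed to nor quantified cannot support the stated 80%.

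*That the H2 allowance shows the authors expected 10% to 20% loss for H1.* The H2 percentages concern scan refusal and motion, which are specific to imaging. They do not predict loss on videotaped hand assessments, and for that reason the H1 loss rates above are labelled as assumptions. The evidence that some loss is expected comes from the Statistical analyses section.

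*That shared camps make the confidence interval wrong.* The one-arm nesting is real, but its effect rests wholly on an assumed correlation. The description of COMBiT has the same core therapists leading every group, at one venue, with tasks graded for the individual child. This removes some usual sources of variation between groups. Two camps could not estimate a camp variance in any case, and reporting a result conditional on the camps run is a legitimate choice.

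**Conclusion.** The point holds in limited form. The 80% stated for H1 has no margin and is not supported as written, because required and recruited numbers coincide and no 26-week loss is allowed for, although missing follow-up is anticipated. On the stated inputs, two-sided and unadjusted, t-test power is about 77% with complete follow-up, 72% at an assumed 10% loss and 67% at an assumed 20%. The detectable difference moves from the stated 7 to 7.3, 7.7 and 8.2.

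Whether the trial in fact has 80% power cannot be determined from the document. It depends on whether 9 is a raw or residual SD, on whether baseline enters the model, and on a correlation that is not given.

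The camp effect is a note and not part of the main conclusion. At an assumed intraclass correlation of 0.02 to 0.05, power without loss would be 74% to 68%, against 78.5% on the same method without clustering.

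**What to change.** Keep n = 50. State whether the SD of 9 is before or after adjustment for baseline and matching. Then do one of the following:

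- Restate the power for the unadjusted comparison: about 77% with all children evaluable and 72% with 10% loss, with detectable differences of 7.3 and 7.7.
- Commit to the baseline score as a covariate in the primary model and state power for a named correlation: 81% with all children and 76% with 10% loss at r = 0.3, or 88% and 84% at r = 0.5. Give the source of the correlation.

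Optionally, add a sensitivity analysis that inflates the COMBiT-arm variance over a range of assumed intraclass correlations, and describe the main result as conditional on the camps run.

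The cost is a few sentences and, if wanted, one sensitivity analysis. No further children are needed. The unadjusted restatement gives a less favourable power figure, and the adjusted one removes the freedom to leave baseline out of the model.

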### Randomisation

Following baseline assessments, children will be randomised within matched pairs to receive either COMBiT or standard care. To maximise homogeneity of the sample and minimise group differences at baseline, matching in pairs will be completed according to age (12 month bands), gender, and Manual Ability Classification System (MACS) level [30]. Treatment allocation will be recorded on a piece of folded paper inside a concealed opaque envelope. Using a sequence of computer-generated random numbers the number “1” or “2” will be allocated to each member of the pair. As each pair is randomised, they will be allocated the next consecutive envelope, which will be opened by non-study personnel who will read and record the treatment allocation. Study personnel will be informed of group allocation.

### Study procedure

Children will attend either the Royal Children’s Hospital or The University of Queensland in Brisbane for baseline and follow up assessments. Children randomised to COMBiT will participate in a two week day camp during school holidays commencing within one month of baseline assessments. Participants randomised to standard care will be allocated a local therapist and individual therapy sessions will commence within one month of baseline assessments. The experimental design and outcome measures are depicted in Figure 1.

**Figure 1 F1:**
[figure not shown]
CONSORT flow chart for COMBiT trial.

### Study interventions

For the COMBiT day camp group, we plan to provide treatment in groups of 10–15 children over ten days. The initial five consecutive days will focus on mCIMT. After a weekend, BIM will be provided for the next five consecutive days. Therapy will comprise 45 hours direct upper limb training and 10 hours of indirect training in more general gross motor upper limb activities. COMBiT will have a novel circus theme. This intensive COMBiT therapy will be compared to standard care which involves individually tailored therapy in a distributed model for 1.5 hours per week for six weeks. This involves six hours individual therapy with OT/PT and three hours of home program demonstration (nine hours direct UL therapy). The home programs (completed by participants in their home/community environment) will comprise 30 minutes daily home practice six days/week for 12 weeks (36 hours indirect UL therapy). The COMBiT and the standard care programs will have the same dosages of upper limb therapy (COMBIT: 45 hours direct UL training; Standard care (SC): nine hours direct UL training and 36 hours indirect UL therapy). They will differ by (i) delivery method (block, group model versus distributed individualised model) (ii) varied construct (mCIMT versus goal directed training) and (iii) different environment.

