#### ***Study duration***

Children will be recruited in blocks of 24 to 26 children at six monthly intervals to enable sessional testing of fMRI and training. The children will attend day camps during a holiday period. Recruitment will take 12 months, as suitable candidates could be drawn from our QCPRRC register (n=180 potential children). Potential participants can receive upper limb intramuscular BoNT-A injections prior to study entry as part of clinical practice. Entry into the study will be delayed for six weeks post injection for those whom have received intramuscular BoNT-A injections in the forearm to reduce spasticity.

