## Statistical analyses

Analysis will follow standard principles for RCTs, using two-group comparisons on all participants on an intention-to-treat basis. Primary analyses will include all evaluable data. Sensitivity analyses will use imputation techniques to account for potential bias as a consequence of non-ignorable missing data during follow-up. The primary comparison H^1^ at 6 months will be based on the AHA and MUUL scores and will be between treatment groups using generalized linear models, with terms included to account for matching and, potentially, confounding variables such as baseline unimanual capacity. Secondary analyses will use similar methods to compare the outcomes between groups for participation (domains of LIFE-H) and QOL (domains of CP-QOL). Where continuous data exhibit skewness not overcome by transformation, non-parametric methods (e.g. Mann–Whitney U Test) will be used for simple comparisons.

For H^2^: The magnitude of central neurovascular changes between groups will be determined using quantitative analysis of fMRI statistical parametric maps will be performed using *iBrain*™: regions of interest will be delineated for each individual (primary motor cortex PM1, supplementary motor area (SMA), and ipsilateral motor cortex (PM1ipsi) and active voxels in those regions will be counted. These data will be compared for each region over time using generalised estimating equations approach. In subjects where mirror movements did not occur, lateralisation between ipsilateral and contralateral PM1 will be assessed using an objective approach^CIC#188^ to determine the incidence and magnitude of brain reorganisation. Statistical significance will be at p<0.05.

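### COMBiT is delivered in about two camps and standard care individually, yet the primary model and the sample size make no allowance for camp, so the standard error may be too small

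*Protocol article*

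**What the plan says.** All references are to the Protocol article.

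- **Delivery of COMBiT.** Study interventions: "we plan to provide treatment in groups of 10–15 children over ten days". The COMBIT subsection describes a shared day programme at one circus venue, in which children help one another with two-handed tasks during the constraint week.
- **Delivery of standard care.** Study procedure and the standard care subsection describe individual sessions with a local therapist plus a home programme.
- **Recruitment and allocation.** Study duration: "Children will be recruited in blocks of 24 to 26 children at six monthly intervals", with recruitment lasting 12 months. Randomisation: "children will be randomised within matched pairs to receive either COMBiT or standard care".
- **Primary model.** Statistical analyses plans generalized linear models for the two primary scores at six months, "with terms included to account for matching and, potentially, confounding variables such as baseline unimanual capacity". Neither camp nor therapy group is named. The generalised estimating equations in the same section are for fMRI regions over time.
- **Sample size.** It is set for the "comparison between the functional effects of COMBiT compared to standard care at 26 weeks": "Based on a comparison with alpha = 0.05 and 80% power, 25 subjects in each group (n=50) are required". No ICC or design effect appears.

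**The concern.** The trial is partially nested: children in one arm are treated together in a few groups, and children in the other arm are treated singly. Anything that differs from one camp to the next and affects outcome makes camp-mates more alike than two COMBiT children chosen at random. Candidates are the mix of peers, the holiday period, day-to-day changes to the programme, and possibly the circus trainers.

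An analysis that treats the 25 COMBiT children as independent then credits that arm with more information than it holds. The interval for the primary comparison would be too narrow, and one unusually good or poor camp, supplying about half the arm, could be read as a treatment effect. This matters because the Background looks beyond these camps, to COMBiT as a model of care.

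**Working it through.** **Inputs.** Difference 7 units on the Melbourne Assessment (MUUL), SD 9, alpha 0.05 (taken as two-sided), power 80%, 25 per arm (Sample size). Camp size: half of 24 to 26 is 12 to 13, so m = 12.5, and 25/12.5 = 2 camps. This number of camps is inferred, not stated. The ICC is an assumption: 0.01 to 0.10. The SD of 9 is taken as the total SD in each arm. The documents give no planning difference or SD for the Assisting Hand Assessment, so the figures are for MUUL.

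**Step 1: reproduce the plan's figure.** n per arm = 2 × [9 × (1.960 + 0.842)/7]² = 25.95, rounded up to 26, against 25 stated. At 25 per arm, SE = 9 × √(2/25) = 2.546 and power = Φ(7/2.546 − 1.960) = Φ(0.790) = 78.5%. The stated size is therefore essentially that for independent children, with no allowance for clustering.

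**Step 2: cluster the COMBiT arm only.**

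- Design effect in that arm: DE = 1 + (m − 1) × ICC = 1 + 11.5 × ICC
- Variance ratio for the difference: R = (DE + 1)/2
- Correct SE = 2.546 × √R
- Type I error of the unadjusted test = 2 × [1 − Φ(1.960/√R)]
- Power at the correct SE = Φ(7/SE − 1.960)

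| Assumed ICC | DE | R | Correct SE | SE larger by | Type I error | Power | n per arm for 80% |
|---|---|---|---|---|---|---|---|
| 0 | 1.000 | 1.000 | 2.55 | 0% | 5.0% | 78.5% | 26 |
| 0.01 | 1.115 | 1.058 | 2.62 | 2.8% | 5.7% | 76% | 28 |
| 0.02 | 1.230 | 1.115 | 2.69 | 5.6% | 6.3% | 74% | 29 |
| 0.05 | 1.575 | 1.288 | 2.89 | 13.5% | 8.4% | 68% | 34 |
| 0.10 | 2.150 | 1.575 | 3.20 | 25.5% | 11.8% | 59% | 41 |

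The last column holds camp size fixed. Over the full planned camp size of 10 to 15, type I error at ICC 0.05 runs from 7.7% to 9.2%.

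**Step 3: does the matching term remove it?** Only the COMBiT member of a pair attends a camp, so the camp effect stays in each within-pair difference and is common to all pairs whose COMBiT child attended that camp. A simulation of 40,000 trials with camps of 13 and 12, analysed by a paired t-test, gave:

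| Within-pair correlation (assumed) | ICC | Mean model SE | True SE | Type I error |
|---|---|---|---|---|
| 0 | 0 | 2.52 | 2.54 | 4.9% |
| 0 | 0.05 | 2.50 | 2.87 | 8.0% |
| 0 | 0.10 | 2.49 | 3.19 | 11.7% |
| 0.3 | 0 | 2.11 | 2.12 | 4.8% |
| 0.3 | 0.05 | 2.09 | 2.53 | 9.7% |
| 0.3 | 0.10 | 2.07 | 2.89 | 14.9% |

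The paired test holds its level at ICC 0, so the inflation comes from camp alone. Useful matching makes it somewhat worse in relative terms: the pair term shrinks the model SE while the camp variance stays in full.

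**The case against.** The case for a small effect is serious.

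- **No ICC is given.** At 0.01 to 0.02 the SE is only about 3% to 6% too small, and at zero it is right.
- **Much of the delivery is common to all camps.** The COMBIT subsection has the same core team plan and lead every group, at a single named venue. What is the same in every camp is part of the treatment and creates no correlation within a camp.
- **Other features point the same way.** There is one trainer for every two children, with individual goals and grading. The primary time point is 26 weeks, long after a two-week camp, and children resume their usual therapy after week 13. Both primary measures are scored from video by masked raters.
- **The list of model terms is open.** Confounders are mentioned only as a possibility and by example, and an analysis plan that is not shown may deal with camp.
- **Clustering may not be confined to COMBiT.** Standard-care children could share a local therapist; the documents do not say how many do.
- **The power figures are for an unpaired, unadjusted comparison,** which is not the planned model.

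These points limit the size of the problem but do not remove it. Peer mix, holiday period and programme changes still differ between camps, and nothing in the article justifies assuming a correlation of exactly zero. The article itself names the model terms and an independence-based sample size, and neither fits the group delivery that it describes.

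A reader might infer that the standard error is certainly too small, that the model adjusts for matching and nothing else, or that shared therapists and setting drive the correlation. The documents support none of these: the ICC is unknown, the covariate list is open, and the core therapists and venue are the same throughout.

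**Conclusion.** The point holds in conditional form. Under any positive within-camp correlation, the primary analysis as described gives intervals that are too narrow, and matching does not repair this. The size is uncertain: negligible to modest at an ICC of 0.01 to 0.02 (type I error 5.7% to 6.3%), and material at 0.05 to 0.10 (8.4% to 11.8%, with power of 68% to 59% against 78.5%).

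These figures assume about two camps of 12.5 children, clustering in the COMBiT arm only, a total SD of 9 in both arms and, for power, an unpaired comparison. No figure in the documents favours one ICC over another, so none of the rows can be called the expected case. The design is not invalid; the plan should make the uncertainty visible.

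**What to change.** Keep the primary model. With two camps, a random effect for camp has about one degree of freedom, so adding that term would not estimate the ICC and would not by itself repair the inference. Instead, add the following to Statistical analyses:

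1. State that the design is partially nested, with camp as the group in the COMBiT arm.
2. Pre-specify a sensitivity analysis of both primary outcomes that multiplies the COMBiT-arm variance by 1 + (m − 1) × ICC, for ICC from 0.01 to 0.10, using the actual camp sizes. In practice this adds (m − 1) × ICC × SD²/n to the squared model SE, with n the number of COMBiT children.
3. Report the largest ICC at which the primary conclusion still holds. As an illustration in the unpaired case, suppose an observed difference of 6 units with the planned SD. It stays significant while SE ≤ 6/1.960 = 3.061, so SE² ≤ 9.371. The unclustered SE² is 6.48 and each unit of ICC adds 11.5 × 81/25 = 37.26, so the limit is (9.371 − 6.48)/37.26 = 0.078.
4. Show the treatment effect by camp.
5. Word any generalisation beyond these camps according to items 3 and 4. Set no fixed ICC as a pass mark, since the documents offer no basis for one.

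The cost is one extra analysis and a paragraph of text, with no extra children, data or staff. The downside is wider intervals in the sensitivity analysis.
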